### Criteria for discontinuing or modifying allocated interventions {11b}

Based on the following baseline laboratory abnormalities, participants may be withdrawn early (late exclusion) from the trial:DAIDS grade 4 neutropenia (absolute neutrophil count <0.4 × 10^9^/L)DAIDS grade 4 renal impairment (absolute creatinine level of ≥400 µmol/L)Microbiological evidence of cryptococcal meningitis, e.g. positive culture or microscopy, where participant was enrolled on a (presumed false) negative cerebrospinal fluid CrAg test

In the above scenarios, all study medication (regardless of treatment arm) is stopped, and the participant is referred to routine care for ongoing treatment.

If a participant is eligible and remains on the trial, study medication may be dose-adjusted or stopped under the following conditions:If a participant withdraws consent to continue study treatment, they are referred to routine care for ongoing treatment of their antigenaemia and HIV.If a participant experiences toxicity thought by the investigator to be related to study medication, the dose may be modified according to clearly defined guidelines in the study work practice documents. Fluconazole doses may be halved, and flucytosine doses may be halved (dosed twice daily) and then reduced further (daily dosing) if needed, with toxicity closely monitored and the dose adjusted up again as soon as possible. For cases in which intolerable toxicity persists despite dose reduction, study medication may be stopped. Alanine transaminase (ALT), renal function and a full blood count with differential are checked at baseline, and full blood count with differential is routinely repeated at day 15. Any abnormalities on day 1 guide additional ad hoc testing at the discretion of the clinician, guided by the work practice documents.As both drugs are renally excreted, baseline renal function guides dosing. If the eGFR (by Cockcroft Gault formula) is <50 ml/min, the fluconazole and flucytosine doses are halved. If the eGFR is <10 ml/min, the flucytosine dose is quartered.

At any time during the study, if a participant develops incident cryptococcal meningitis (not present at baseline), study medication is stopped and the participant is referred to routine care for treatment of their cryptococcal meningitis, though study follow-up continues per protocol.

If a participant becomes pregnant during the intervention period, study medication is stopped immediately and the participant is referred for appropriate antifungal therapy and antenatal care. These participants are followed up beyond the standard 6-month follow-up period to assess pregnancy outcomes.

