**Clinical labs**																				
HIV testing*^	X																			
CrAg test*^	X																			
CD4 count*^	X																			
Pregnancy test (urine/serum)*^ (1)	X																			
Cerebrospinal fluid testing*^	X																			
Full blood count with differential		X														X				
Serum creatinine		X																		
Serum alanine transaminase		X																		
Urine lipoarabinomannan* (3)	X	(X)																		

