**Research samples—stored at −80 °C**																				
Serum/plasma (5 ml)		X														X				
Whole blood (5 ml)		X																		
Urine (2 ml)		X																		
CSF (2 ml)**	(X)	X																		

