Analyses of survival data will be conducted using unadjusted and adjusted Cox regression analysis to calculate the hazard ratio (HR) and 95% CI between the treatment groups. Kaplan-Meier survival curves will also be plotted by treatment group, from which survival rates at 10 weeks and 6 months will be derived. A log-rank test will be performed to compare the survival curves between the treatment groups.

Primary analyses of efficacy outcomes will be based on the intention-to-treat population, and secondary analyses will be based on the per-protocol population. The safety analysis will be on the safety population. The frequency and proportions of participants developing clinical and laboratory-defined side effects (DAIDS grade 3 or 4 adverse events) will be summarised by treatment arm.

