### Adverse event reporting and harms {22}

At enrolment, a detailed medical history (including history of exposure and adverse reactions to study medication) and clinical examination are undertaken, and baseline laboratory tests (ALT, creatinine and full blood count with differential) are performed. Any abnormal findings are recorded and graded in line with DAIDS grading conventions. Any worsening from baseline or any new abnormality arising after enrolment until 6 months of follow-up is complete is considered an adverse event. DAIDS grade 1 or 2 adverse events are recorded only in clinical notes but grade 3 or 4 events, as well as all deaths (grade 5), are reported in the EDC system. The severity of the event is determined by the clinical investigator, who also makes an assessment of causality and expectedness as well as seriousness, i.e. whether the event meets criteria for a serious adverse event (SAE) as per ICH-GCP. Non-serious adverse events are reviewed by the relevant site PI and the lead clinician while serious adverse events are reviewed by an additional clinically trained TMG member experienced in the management of this population. The TMG reviewer completes a review form in the EDC indicating their agreement with the site investigator’s assessment. In cases of death, a second TMG member provides additional review and assessment of causation, specifically whether the death is likely due to cryptococcal meningitis.

All adverse events are followed up until resolution or until the participant completes study follow-up, dies or withdraws. Study staff, regardless of whether the event is considered related to study product, facilitate appropriate referral for treatment of the adverse event as necessary.

All adverse events and deaths are reviewed by the DMC and reported to the local regulatory authority and research ethics committee in line with their reporting requirements.

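### Creatinine and ALT are scheduled only on day 1, so the renal and hepatic part of the laboratory-defined grade 3/4 endpoint rests on discretionary testing by clinicians who know the arm

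*Protocol article*

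**What the plan says.** Protocol section {11b} has ALT, renal function and a full blood count checked at baseline, and then states that "full blood count with differential is routinely repeated at day 15". For anything further, the rule is: "Any abnormalities on day 1 guide additional ad hoc testing at the discretion of the clinician", with the work practice documents as guidance. The event schedule in section {13} agrees: the full blood count is marked at day 1 and day 15, while the rows for "Serum creatinine" and "Serum alanine transaminase" carry a single mark, at day 1. Under section {18b}, contact after day 15 is by telephone unless there is a clinical reason for a visit.

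The endpoint covers more than the schedule measures. Section {12} lists the proportions with clinical and laboratory-defined DAIDS grade 3 or 4 events as a secondary outcome, and section {20a} has these summarised by arm. Section {22} sets the window: "Any worsening from baseline or any new abnormality arising after enrolment until 6 months of follow-up is complete is considered an adverse event". Section {20c} defines the safety population as participants in the intention-to-treat analysis with at least one day of study treatment; having a post-baseline laboratory value is not a condition.

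The trial is open-label ({17a}, {17b}), and the protection against bias offered in {17a} is the objective mortality endpoint. Section {13} also has serum or plasma stored from both arms at day 1 and day 15.

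**The concern.** A laboratory-defined event can be counted only if a sample is taken. After day 1 no creatinine or ALT sample is planned for anyone, so each later value exists because someone outside the fixed schedule ordered it. Two consequences follow. First, events may be missed in both arms, which understates absolute renal and hepatic rates and weakens the ability to see a real difference. Second, the person ordering the test knows whether the participant is taking the added drug. If that knowledge changes how readily tests are ordered, the between-arm comparison mixes testing intensity with harm.

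This matters because the abstract's discussion presents the combination as potentially safe and easy to administer, and the introduction anticipates out-patient use with few adverse events. A low renal or hepatic count produced by little testing would wrongly support that message; uneven testing could wrongly undermine it. The argument about an objective mortality endpoint does not extend to this safety outcome.

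**Working it through.** **The plan's own figures.** The protocol gives no expected rate, testing share or power for the safety endpoint, so there is nothing to reproduce on this point. Its sample-size figures are not in dispute: with 270 per arm and two-sided 0.05, the usual two-proportion formula gives 90.6% for 30% vs 18% (stated 91%), and 540/0.9 = 600.

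**Schedule against endpoint.**

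| Laboratory component | Day 1 | Day 15 | After day 15 | Counted in endpoint until |
|---|---|---|---|---|
| Full blood count with differential | scheduled | scheduled | unscheduled | 6 months |
| Creatinine | scheduled | unscheduled | unscheduled | 6 months |
| ALT | scheduled | unscheduled | unscheduled | 6 months |

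Haematology has one common post-baseline time point in both arms. Creatinine and ALT have none.

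**Unequal testing, no true difference (all inputs assumed).** Let t be the true grade 3/4 creatinine/ALT rate, equal in both arms, and s the share tested. Suppose testing is unrelated to having an event and untested events go unseen. Then

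observed rate = t × s, and observed RR = (t × s_int)/(t × s_ctrl) = s_int/s_ctrl, whatever the value of t.

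| Tested, control vs intervention | Observed RR |
|---|---|
| 30% vs 30% | 1.00 |
| 30% vs 50% | 0.50/0.30 = 1.67 |
| 20% vs 40% | 0.40/0.20 = 2.00 |
| 50% vs 30% | 0.30/0.50 = 0.60 |

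The last row shows that the direction is not fixed either.

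**Dilution in a laboratory composite (assumed).** Let haematology events occur at rate h in both arms, be fully observed and be independent of renal/hepatic events. Then observed composite = 1 − (1 − h)(1 − t × s). Take t = 5% and testing of 30% vs 60%, so the creatinine/ALT RR alone would be 2.0:

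- h = 5%: control 1 − 0.95 × 0.985 = 6.43%; intervention 1 − 0.95 × 0.97 = 7.85%; RR 1.22.
- h = 10%: 11.35% vs 12.70%; RR 1.12.
- h = 15%: 16.28% vs 17.55%; RR 1.08.

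**Equal but sparse testing, real harm (assumed).** Take true rates of 5% control and 10% intervention with n = 300 per arm and two-sided 0.05:

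power = Φ{ [ |p1 − p2| − 1.96 √(2 p̄(1 − p̄)/n) ] / √( [p1(1 − p1) + p2(1 − p2)]/n ) }.

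- Everyone tested, 10% vs 5%: (0.05 − 1.96 × 0.02151)/0.02141 = 0.37, power 64%.
- 30% tested in each arm, observed 3.0% vs 1.5%: (0.015 − 1.96 × 0.01211)/0.01209 = −0.72, power 24%.

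So balanced testing removes the spurious difference but still leaves a real one hard to see.

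**The case against.** The strongest reply is that the discretion is bounded. The stated trigger is a day-1 abnormality, which randomisation should balance, and testing follows work practice documents that are not shown. This stands in part: arm-dependent testing is possible but not demonstrated. It does not remove the point, because the decision still lies with a clinician who knows the arm, and no retest is scheduled for anyone, including participants with normal day-1 values.

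A second reply is that denominators and handling of absent laboratory values belong to the SAP, and that {20a} says only that these events will be summarised by arm. This is fair as far as it goes. The general rule in {20a} that binary secondary endpoints receive a relative risk could be read to include safety, but no separate test of laboratory events is specified. The measurement schedule itself, however, is fixed in the protocol, and no analysis can supply values that were never taken.

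Four stronger readings are tempting and are not supported:

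- A reader might infer that the whole laboratory comparison depends on whom clinicians test. It does not: the blood count is scheduled at day 15 in both arms, and the endpoint also includes clinical events.
- A reader might infer that detection does differ by arm. The documents show only that it could. Renal dose adjustment in {11b} applies to both drugs, and the protocol describes the combination as well tolerated.
- A reader might infer that untested participants will be counted as event-free. The treatment-based safety population makes that possible, but the protocol does not state it.
- A reader might infer that, with 20% tested, 80% of events are missed. That treats testing as unrelated to illness. If ill participants are tested more readily, fewer events are missed.

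**Conclusion.** The point holds for creatinine and ALT. The renal and hepatic part of the laboratory-defined grade 3/4 endpoint has no scheduled post-baseline measurement; it can be under-detected in both arms and may be detected unequally. Haematology is largely unaffected, apart from counts taken at unscheduled times, and the mortality primary endpoint is not affected.

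The size cannot be calculated from the documents. The relative risks of 1.67 and 2.0 for creatinine/ALT events, and of about 1.08 to 1.22 for a composite with haematology, rest on assumed testing shares and event rates, on equal true rates, and on testing unrelated to events. They illustrate the mechanism and do not predict a result. This is a cheap improvement to the safety reporting and does not put the trial's main conclusion at risk.

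**What to change.** Keep the planned summary of all grade 3 or 4 events, and add the following:

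1. A between-arm laboratory comparison restricted to protocol-scheduled tests, that is, the day-15 full blood count, with participants sampled as the denominator.
2. Separate reporting of unscheduled creatinine and ALT events, with the number tested in each arm and a statement that they are not to be read as an unbiased comparison.
3. Where storage consent ({26b}) and sample volume allow, and subject to analyte stability, measurement of creatinine and ALT in the day-15 serum or plasma stored from both arms. This would give a common post-treatment value and remains possible after recruitment, which was expected to finish in October 2025.

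The first two items cost only analysis-plan wording. The third costs a batch assay, covers only consenting participants sampled at day 15, and may compete with the sub-studies in {33}. The scheduled-test comparison will contain fewer events and, without the assay, no renal or hepatic ones; for that reason it should supplement the all-events summary and not replace it. No change to clinical monitoring is proposed.

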### Strategies to improve adherence to interventions {11c}

All participants undergo extensive adherence counselling at baseline, including education about cryptococcosis and the importance of adequate antifungal therapy.

Fluconazole is dosed once daily and the timing of this dose is tailored to the participant’s needs, e.g. timing of other medication and work schedule.

Flucytosine is dosed 4 times daily approximately 6 h apart. Participants are asked to complete a medication diary in which they mark off each dose taken.

At days 3 and 9, telephonic follow-up includes adherence counselling and self-reported pill counts.

### Relevant concomitant care permitted or prohibited during the trial {11d}

The trial protocol prohibits the concomitant use of cisapride and the class of antihistamines including terfenadine. Participants receiving these drugs during study screening are excluded. All other medications are allowed, with careful consideration of drug-drug interactions and shared toxicity profiles. Importantly, participants should continue their full package of advanced HIV care, including prophylaxis and treatment for other conditions.

### Provisions for post-trial care {30}

Although the trial intervention is the induction phase (first 14 days of antifungal therapy), the study provides fluconazole consolidation treatment through week 10, to ensure adequate supply to all participants and avoid the impact of potential stock-outs in routine care. In cases in which no routine fluconazole is available, the study may also provide maintenance fluconazole to month 6. Fluconazole maintenance therapy is indicated for varying durations depending on local guidelines (at least 12 months) and is generally widely available at trial sites.

Study participants who develop cryptococcal meningitis during follow-up are treated by routine care; however, if any of the antifungal drugs required are not available, the study provides these. The Trial Management Group is involved in ongoing advocacy for flucytosine access for cryptococcal meningitis in routine care settings.

### Outcomes {12}

#### Primary

All-cause mortality at 6 months after randomisation (proportion, relative risk)—the use of this primary outcome was decided on as a means of minimising bias, given that the trial is open-label.

Justification: If the all-oral combination intervention regimen is found to be superior to the standard of care, this could reduce mortality among individuals who screen positive for cryptococcal antigenaemia without the need for hospital admission. All-cause mortality at 6 months was chosen as the primary outcome for the trial because compared to cryptococcal disease-specific mortality, this endpoint avoids problems such as missing data and changes in disease classification over time. In addition, ascertainment of cause of death among people with advanced HIV disease is difficult based purely on verbal autopsy or record review, with the possibility of multiple co-morbid conditions, some of which may not have been diagnosed ante-mortem.

#### Secondary

Time to all-cause mortality within first 6 months, presented in Kaplan-Meier curves per treatment groupAll-cause mortality at 10 weeks (proportion, relative risk)—sensitivity analysis will also be performedTime to all-cause mortality within the first 10 weeks, presented in Kaplan-Meier curves per treatment groupCryptococcal meningitis-free survival to 6 monthsIncidence rate of symptomatic cryptococcal meningitis over 6 months—number of events and incident rate by treatment groupCryptococcal-related mortality at 6 months (proportion, relative risk)Tolerability and safety: proportions of participants developing clinical and laboratory-defined DAIDS grade 3 or 4 adverse eventsEfficacy outcomes (10-week and 6-month mortality) by baseline blood CrAg titre/CrAg semi-quantitative (SQ) assay scoreRates of disability at 6 months (using modified Rankin scores)—generalised odds ratioHealth service and household costs per life year saved, including annualised health care cost, cost per disability-adjusted life years (DALYs) averted and life years lost, cost offsets and household financial burden per individual.

### Participant timeline {13}

**Table Tabb:** 

Event schedule	Screening	Week 1							Week 2								Mth 1	Mth 2.5	Mth 4	Mth 6
Study day	≤D0^~^	D1^~^	D2	D3	D4	D5	D6	D7	D8	D9	D10	D11	D12	D13	D14	D15				
**Consent forms**																				
PIS and signed consent	X	X																		
**Follow-up**																				
Screening	X	X																		
Randomisation		X																		
Clinical review		X														X				
Telephone follow-up				X						X							X	X	X	X
**Clinical labs**																				
HIV testing*^	X																			
CrAg test*^	X																			
CD4 count*^	X																			
Pregnancy test (urine/serum)*^ (1)	X																			
Cerebrospinal fluid testing*^	X																			
Full blood count with differential		X														X				
Serum creatinine		X																		
Serum alanine transaminase		X																		
Urine lipoarabinomannan* (3)	X	(X)																		
**Clinical evaluation**																				
Chest X-ray (2)		X																		
**Research samples—stored at −80 °C**																				
Serum/plasma (5 ml)		X														X				
Whole blood (5 ml)		X																		
Urine (2 ml)		X																		
CSF (2 ml)**	(X)	X																		
**Induction therapy: intervention**																				
Fluconazole plus flucytosine		X	X	X	X	X	X	X	X	X	X	X	X	X	X					
**Induction therapy: control**																				
Fluconazole alone		X	X	X	X	X	X	X	X	X	X	X	X	X	X					

1. For women of childbearing age

2. If clinically indicated (e.g. symptoms of pulmonary tuberculosis). Sputum TB tests will also be performed if clinically indicated, as per national guidelines

3. Urine LAM may be omitted in participants known with TB/on TB treatment

*Part of routine care

^Required for inclusion

^~^Practically, screening and day 1 visit commonly occur on 1 day

**Collected either on D1 or if available, with consent, from routine lumbar puncture CSF sample (also to be collected and stored if participant presents later with symptomatic CM)

### Sample size {14}

Based on evidence from recent studies, we assume that the combined regimen of fluconazole plus flucytosine (intervention arm) could lead to a 40% relative reduction in mortality compared with fluconazole alone. From the ACTA trial [2, 31], the oral combination treatment had a mortality rate of 35% at 10 weeks, compared with 55%–70% mortality of fluconazole alone observed in clinical settings (i.e. a reduction of at least 36% mortality). We assume that 30% of blood CrAg-positive individuals identified during screening and treated with fluconazole alone die. This assumption is inferred from published data, including the REMSTART trial [15] in which 32% of blood CrAg-positive individuals treated with fluconazole (CD4 < 200 cells/µl) died over 6 months of follow-up. In South Africa, mortality was 25% in 2 cohort studies [16, 17].

Using a two-sided *α* = 0.05, a sample size of 540 (270 per arm) will provide 91% power to detect a 40% relative reduction in mortality with fluconazole alone versus flucytosine plus fluconazole (i.e. an observed mortality of 30% vs. 18%, respectively). The trial will also have 81% power to detect a 35% relative reduction if the effect size is smaller, and 83% power if mortality in the fluconazole arm is lower at 25%. Loss to follow-up was 2.5% in the REMSTART trial [15] over 12 months and <1% in the ACTA trial [2] over 10 weeks. A target of 600 participants will be enrolled, to conservatively account for up to 10% loss to follow-up in a pragmatic trial embedded in routine programmes.

### Recruitment {15}

Potentially eligible individuals are identified through local CrAg screening programmes, that is individuals who are HIV-seropositive, have a CD4 count of <100 cells/ml and are blood CrAg-positive. In South Africa, trial staff receive an electronic list of all CrAg-positive results from the national laboratory and from this list, identify potential candidates. In Tanzania, routine staff who receive a CrAg-positive result on their clients refer them to the trial teams at the sites. These individuals are considered by study staff for screening and possible enrolment on the trial and may be contacted and invited to attend a screening visit, during which appropriate screening tests are performed (such as lumbar puncture and urine pregnancy test); these are part of the local CrAg screening programme and not study-specific procedures, but if these have not yet been done by routine care, study staff offer these. Study staff do not routinely repeat blood CrAg testing. During this process, the purpose of these procedures is explained to the individual, in the context of routine care and with reference to the trial. If the individual is found to meet all inclusion criteria and no exclusion criteria, then they are invited to participate in the trial and informed consent is obtained.

